### Efficacy evaluation criteria

① Primary Efficacy Outcome Measures

The primary efficacy outcome is the successful discontinuation rate of NBZDs at the end of the 6-week treatment period. Between-group differences in discontinuation rate will be evaluated using regression-based methods appropriate for binary outcomes.

② Secondary Efficacy Outcome Measures

a. Subjective Sleep Efficacy Evaluation

Subjective sleep outcomes, including the Insomnia Severity Index (ISI) and Pittsburgh Sleep Quality Index (PSQI), will be analyzed using longitudinal mixed-effects models incorporating repeated measurements across predefined study time points to estimate treatment effects over time.

b. Objective Sleep Efficacy Assessment

Objective sleep parameters derived from PSG and ACT will be analyzed using longitudinal mixed-effects models to account for within-subject correlation and to evaluate changes across study time points.

c. Daytime Functioning Assessment

Daytime functioning outcomes will be analyzed using longitudinal mixed-effects models to assess treatment effects across time.

d. NBZDs Reduction Response Evaluation

Medication reduction responses, including NBZDs reduction rate, withdrawal symptoms, and craving scores, will be evaluated using regression-based models appropriate to outcome type, with longitudinal modeling applied where repeated measurements are available.

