**Methods:**

This single-blind, randomized, controlled trial will enroll 78 adults with chronic insomnia disorder (ICSD-3TR) who have used NBZDs for >6 months. Participants will be assigned 1:1 to electroacupuncture or sham electroacupuncture. Both groups will undergo a standardized, gradual NBZDs tapering protocol over 6 weeks and receive standardized sleep hygiene education. Participants in the electroacupuncture group will receive electroacupuncture treatment three times per week at predefined acupoints (Baihui, Sishencong, Anmian, Shenting, Yintang, Hegu, Taichong, Neiguan, Shenmen, Sanyinjiao, Shenmai, and Zhaohai), whereas participants in the control group will receive non-penetrative sham electroacupuncture. The primary outcome is the successful discontinuation rate of NBZDs at the end of the 6-week treatment period. Secondary outcome measures included subjective sleep scales, objective sleep parameters (polysomnography and actigraphy), and daytime functioning assessments, among others. Safety will be assessed through systematic monitoring and documentation of adverse events. Statistical analyses will follow the intention-to-treat principle using mixed-effects models.

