### Sample size

The expected discontinuation efficacy rate for the sham acupuncture group in the sample size calculation was derived from a randomized controlled trial that enrolled 144 long-term benzodiazepine users (21). However, this trial yielded a negative result, which might be attributable to the simultaneous inclusion of both BZDs and NBZDs in the study medication (22). Therefore, only the sham acupuncture group discontinuation rate of 10.83% was adopted from that trial, while the expected successful discontinuation rate for the acupuncture group was based on our pilot study.

A pilot study was conducted at our center prior to the main trial to assess the feasibility of the intervention and to obtain preliminary estimates of effect size. Ten eligible patients with chronic insomnia disorder who had used NBZDs regularly for >6 months received electroacupuncture (three times per week for 6 weeks) combined with the standardized 6-week NBZD tapering protocol (25% dose reduction every week). The successful discontinuation rate was 50.00% (5/10). No serious adverse events were reported. Detailed pilot study results are provided in Supplementary Appendix S2.

Based on expected outcomes and relevant published literature (21), this study hypothesized that after treatment, the discontinuation efficacy rates of NBZDs at 6-week post-treatment for the electroacupuncture group and sham needle and sham electroacupuncture group would be 50.00 and 10.83%, respectively. This study set *α* = 0.05 and 1-*β* = 0.90, employing a two-sided test with equal sample sizes between treatment and control groups. Referencing the sample size estimation formula for comparing efficacy rates between two groups from Sun Zhenqiu’s Medical Statistics, the calculation formula was as follows:

$$n=1641.4/{\left[\frac{\left(u_{\alpha }+u_{\beta }\right)}{\sin^{-1}\sqrt{P_{1}}-\sin^{-1}\sqrt{P_{2}}}\right]}^{2}$$

where 
$u_{\alpha }$
=1.96 (for 
α
=0.05, two-sided), 
$u_{\beta }$
=1.282 (for 
β
=0.10), P_1_ = 50.00%, and P_2_ = 10.83%. The calculation yields n = 31.7 ≈ 32 cases. Accounting for dropout rates, the clinically set dropout rate is 20%, resulting in a final sample size of 39 participants per group, totaling 78 participants across both groups.

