### Statistical analysis

All statistical analyses will be conducted using SPSS version 28.0 (IBM Corp., Armonk, NY, United States) according to the intention-to-treat principle. A two-sided *p* < 0.05 will be considered statistically significant.

Continuous variables will be summarized as mean ± standard deviation or median (interquartile range), as appropriate. Categorical variables will be presented as frequencies and percentages. Between-group differences at single time points will be assessed using independent-samples *t*-tests or Mann–Whitney U tests for continuous variables and *χ*^2^ or Fisher’s exact tests for categorical variables.

Longitudinal outcomes will be analyzed using linear mixed-effects models with fixed effects for group, time, and group-by-time interaction, and random intercepts for participants. Missing data will be handled using likelihood-based estimation under the missing-at-random assumption. Multiple imputation will be conducted as a sensitivity analysis.

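### The primary outcome has two unreconciled analyses, and the longitudinal model as written gives a change-score contrast where adjusting for baseline would be more precise

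*Protocol article*

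**What the plan says.** The primary outcome is binary: no NBZD use in days 36–42. Table 1 schedules it once, at week 6. Two sections of the protocol article bear on its analysis.

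- Efficacy evaluation criteria, which is specific to the primary outcome: "Between-group differences in discontinuation rate will be evaluated using regression-based methods appropriate for binary outcomes". No model, effect measure or covariate is named.
- Statistical analysis, which is general: "Between-group differences at single time points will be assessed using independent-samples" t-tests or Mann–Whitney tests when the variable is continuous, and by chi-square or Fisher's exact tests when it is categorical. There is no rule for choosing between the last two, and this section mentions no regression for a binary outcome.

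The Abstract adds a general line: "Statistical analyses will follow the intention-to-treat principle using mixed-effects models".

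For repeated measures, Statistical analysis specifies "linear mixed-effects models with fixed effects for group, time, and group-by-time interaction, and random intercepts for participants". Baseline is not listed as a covariate. Table 1 schedules week 0 for ISI, PSQI, ESS, FSS, GAD-7, PHQ-9, VAS, PSG and actigraphy, among others, but not for BHWSS.

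**The concern.** A once-read binary outcome falls under both the specific and the general statement, and these lead to different p-values. Even regression is not a single p-value, since Wald and likelihood-ratio tests differ in small samples. If the choice is left open until the data are seen, a borderline trial could be called positive or negative at will.

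The second part concerns precision. A model with group, time, their interaction and a random intercept, fitted to data that include week 0, estimates the week-6 effect as a difference in change from baseline. That is valid, but it gives away precision that the collected baseline values would supply at no cost.

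**Working it through.** **Inputs.** Sample size section: "This study set *α* = 0.05 and 1-*β* = 0.90", "employing a two-sided test with equal sample sizes between treatment and control groups"; sham rate, "only the sham acupuncture group discontinuation rate of 10.83% was adopted from that trial"; electroacupuncture rate from the pilot, "The successful discontinuation rate was 50.00% (5/10"; 32 per arm before dropout and 39 after. Visit schedule: Table 1. The smaller effects and the correlation rho used below are assumptions.

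**The plan's own figure.** The continuity-corrected two-proportion formula with p1 = 0.50 and p2 = 0.1083 gives 26.85 before correction and 26.85/4 × [1 + √(1 + 4/(26.85 × 0.3917))]² = 31.75 after it. This matches the stated 31.7 and 32. Then 32 × 1.2 = 38.4, rounded up to 39. (The arcsine formula named in the article gives about 25.9 in its usual form. That is a separate matter.)

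**Can the test decide the result?** Two-sided p-values with 39 per arm:

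| Successes | Chi-square | Fisher | Logistic, Wald | Logistic, LR |
|---|---|---|---|---|
| 14 vs 6 | 0.038 | 0.068 | 0.043 | 0.036 |
| 13 vs 5 | 0.032 | 0.058 | 0.037 | 0.029 |
| 11 vs 4 | 0.044 | 0.083 | 0.052 | 0.041 |

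Yes. In the last row even the two logistic tests fall on opposite sides of 0.05.

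**How often?** Exact enumeration of all 2×2 tables with 39 per arm:

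| True rates | Chi-square rejects | Fisher rejects | The two disagree |
|---|---|---|---|
| 50% vs 10.83% (planned) | 98.1% | 96.3% | 1.8% |
| 40% vs 10.83% (assumed) | 87.2% | 80.9% | 6.3% |
| 35% vs 10.83% (assumed) | 74.7% | 65.9% | 8.8% |
| 30% vs 10.83% (assumed) | 57.4% | 47.2% | 10.2% |
| 10.83% in both arms (null) | 5.8% | 1.8% | 4.0% |

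With 32 per arm at the planned rates, power is 95.2% (chi-square) and 92.0% (Fisher), and the two disagree in 3.2% of trials.

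**Longitudinal model.** Take time as categorical, data as complete, and variance σ² as equal at week 0 and week 6 with correlation rho. The group-by-time term at week 6 is then the between-group difference in mean change.

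- Per-participant variance of change: 2σ²(1 − rho).
- Residual variance after adjusting for baseline: σ²(1 − rho²).
- Ratio, adjusted to change: (1 − rho²) / [2(1 − rho)] = (1 + rho)/2.

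For rho = 0.3, 0.5 and 0.7 the ratio is 0.65, 0.75 and 0.85, so adjustment removes 35%, 25% and 15% of the variance. The documents give no value for rho.

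**Room for covariates in the primary model.** Expected successes are 39 × (0.50 + 0.1083) = 23.7 at the planned rates and 39 × (0.40 + 0.1083) = 19.8 if electroacupuncture reaches only 40%.

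**The case against.** The best defence is that the specific statement governs the general one: regression is the primary analysis, and the chi-square or Fisher sentence is routine text that follows the descriptive summaries. Unadjusted logistic regression and chi-square also test the same null hypothesis, and at the planned effect every test exceeds the stated 90% power. Much of this stands. It makes the two statements unreconciled rather than contradictory, and it limits the practical risk. It does not settle the matter, because the article never says which statement governs and the regression itself is unnamed.

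A reader might infer more than the documents support:

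- *Three incompatible primary analyses.* The Abstract line is a general summary, and Statistical analysis confines mixed models to longitudinal outcomes. It is not a third rule for the primary outcome.
- *No model uses baseline.* Week 0 appears to enter the longitudinal models as a response. What is missing is adjustment for it.
- *The inference on the six-visit scales is an omnibus interaction test on 5 degrees of freedom.* The article does not say so, and the stated model can deliver a week-6 contrast.
- *The primary analysis is known to lose power without covariates.* The wording does not exclude covariates, and any gain depends on an assumed prognostic slope. For 40% vs 10.83% with 39 per arm, simulated power rises from about 88% to 91–93% for a log-odds slope of 0.8–1.2 per SD, but only from 88.1% to 88.8% for a slope of 0.4.

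Firth correction, an unstructured covariance matrix and scaling dose to a guideline maximum are preferences, not corrections of an error. Covariate lists are commonly left to a statistical analysis plan, which is not shown. The longitudinal model is different, because the article itself writes out its terms.

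**Conclusion.** The concern holds in this limited form. Two sections give unreconciled analyses for the primary outcome, and the choice can move a borderline result across 0.05. At the planned rates with 39 per arm that happens in about 2% of trials between chi-square and Fisher. It rises to about 6–10% if the true electroacupuncture rate is 30–40% (assumed), which is plausible given that 50% rests on ten pilot patients. Under the null at 10.83% the two tests also differ in size, 5.8% against 1.8%.

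The longitudinal model is valid but less precise than it could be: adjusting for baseline would save 15–35% of the variance for rho of 0.7–0.3, assuming categorical time, complete data and equal variances. Neither part undermines the trial. Both should be fixed because the remedy is nearly free.

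**What to change.** Before unblinding, amend Efficacy evaluation criteria and Statistical analysis so that they agree.

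1. Name one primary analysis, such as logistic regression of week-6 success on group with baseline weekly NBZD dose and baseline ISI as covariates, reported as a risk difference with 95% CI. State which test gives the p-value. Label chi-square or Fisher as supportive only.
2. For scales and objective measures with a week-0 value, adjust for baseline, either as a covariate or through a common baseline mean, and name the week-6 group contrast as the estimate. BHWSS has no week-0 value, so this does not apply to it.
3. Word the Abstract line so that mixed models refer to the longitudinal outcomes.

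The cost is wording: baseline medication use and ISI are already collected, and no patients or visits are added. The one statistical downside is small: two extra parameters in the primary model with about 20–24 expected successes.

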**Figure 1 fig1:**
[figure not shown]
Flow diagram. ACT, actigraphy; AES, Acupuncture Expectancy Scale; BHWSS, Benzodiazepine Hypnotics Withdrawal Symptom Scale; CSD, Consensus Sleep Diary; ESS, Epworth Sleepiness Scale; FSS, Fatigue Severity Scale; GAD-7, Generalized Anxiety Disorder 7-item; ISI, Insomnia Severity Index; NBZDs, Non-Benzodiazepines; PHQ-9, Patient Health Questionaire-9; PSG, polysomnography; PSQI, Pittsburgh Sleep Quality Index; VAS, Visual Analogue Scale; 5-HT: 5-hydroxytryptamine.

**Table 1 tab1:** Trial processes chart.

Week	0	1	2	3	4	5	6	7	8	9	10
	Baseline	Treatment phase						Follow-up phase			
Patients											
Enrolment	**×**										
Sign informed consent	**×**										
General information	**×**										
Medication diary	**×**	**×**	**×**	**×**	**×**	**×**	**×**	**×**	**×**	**×**	**×**
PSG	**×**						**×**				
ACT	**×**						**×**				
Groups											
Acupuncture group		18 treatments									
Sham- acupuncture group		18 treatments									
Outcome measurement											
Successful drug discontinuation rate							**×**				
CSD	**×**		**×**		**×**		**×**		**×**		**×**
ISI	**×**		**×**		**×**		**×**		**×**		**×**
PSQI	**×**						**×**				**×**
ESS	**×**						**×**				**×**
FSS	**×**						**×**				**×**
GAD-7	**×**						**×**				**×**
PHQ-9	**×**						**×**				**×**
NBZDs reduction rate	**×**		**×**		**×**		**×**		**×**		**×**
BHWSS			**×**		**×**		**×**		**×**		**×**
VAS	**×**		**×**		**×**		**×**		**×**		**×**
AES	**×**										
Blinding assessment		**×**		**×**			**×**				
Adverse events											
Reasons for dropouts or withdrawals	**×**	**×**	**×**	**×**	**×**	**×**	**×**	**×**	**×**	**×**	**×**

ACT, actigraphy; AES, Acupuncture Expectancy Scale; BHWSS, Benzodiazepine Hypnotics Withdrawal Symptom Scale; CSD, Consensus Sleep Diary; ESS, Epworth Sleepiness Scale; FSS, Fatigue Severity Scale; GAD-7, Generalized Anxiety Disorder 7-item; ISI, Insomnia Severity Index; NBZDs, non-benzodiazepines; PHQ-9, Patient Health Questionaire-9; PSG, polysomnography; PSQI, Pittsburgh Sleep Quality Index; VAS, Visual Analogue Scale; 5-HT, 5-hydroxytryptamine.

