### NBZDs tapering protocol

Based on the 2025 European clinical practice guideline recommending a gradual dose reduction of 10–25% per week for NBZDs (27), and supported by two clinical studies that successfully employed a weekly 25% reduction strategy (21, 28), NBZDs will be reduced at a rate of 25% of the baseline dose per week. If participants experience intolerable withdrawal symptoms during tapering—such as exacerbation of insomnia, anxiety, or agitation—the dose will be temporarily reverted to the previous level. Tapering will be reattempted during the subsequent evaluation cycle (1 week per cycle).

Throughout the treatment period, participants will attend weekly in-person consultations and receive twice-weekly telephone follow-ups. Dose adjustments will be conducted through a shared decision-making process, enabling participants to actively engage in symptom monitoring and self-management under physician supervision. Final dosage modifications will require investigator approval.

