#### Secondary outcome measures

Secondary outcomes are assessed at baseline, during treatment, and during follow-up. Detailed assessment procedures are provided in the Supplementary Appendix S1; assessment time points are summarized in Table 1.

(1) *Subjective Sleep Scales*

① Consensus Sleep Diary (CSD): Records total sleep time (TST), sleep onset latency (SOL), wake after sleep onset (WASO), sleep efficiency (SE), subjective sleep quality, and medication use (32–35).

② Insomnia Severity Index (ISI): 7-item scale (0–28) (36); scores ≥15 indicate clinically significant insomnia (37); a reduction of ≥8 points indicates meaningful improvement (38).

③ Pittsburgh Sleep Quality Index (PSQI): Global sleep quality (0–21); scores > 5 indicate poor sleep quality (39–42).

(2) *Daytime Functioning Assessment*

① Epworth Sleepiness Scale (ESS): Daytime sleepiness across eight situations (43, 44).

② Fatigue Severity Scale (FSS): 9-item scale (9–63); scores ≥36 indicate clinically significant fatigue (45–47).

③ Generalized Anxiety Disorder 7-item Scale (GAD-7): Anxiety severity (0–21) (48–50).

④ Patient Health Questionnaire-9 (PHQ-9): Depression symptom severity (51, 52).

(3) *Medication Reduction Response Assessment*

① NBZDs Reduction Rate

The NBZDs reduction rate was calculated using the following formula: NBZDs reduction rate = (Pre-treatment weekly NBZDs dose - Post-treatment weekly NBZDs dose) / Pre-treatment weekly NBZDs dose * 100% (Note: Pre-treatment refers to the baseline period, and post-treatment refers to week 6 of the treatment period) (16).

② Benzodiazepine Hypnotics Withdrawal Symptom Scale (BHWSS): 12-item self-report (3-point scale) assessing withdrawal symptoms (53, 54).

③ Medication Craving Visual Analogue Scale (VAS): 0–10 scale (0 = no craving, 10 = extreme craving) (55).

(4) *Objective sleep assessment parameters*

① Polysomnography (PSG): performed as the primary objective sleep assessment, with all participants undergoing one night of 8-h monitoring during screening to exclude other sleep disorders; sleep stages and parameters were manually scored according to the AASM Manual (Version 3.0) (56–58).

② Actigraph (ACT): Recorded for 7 consecutive days at baseline and at the end of intervention; parameters included number of awakenings (NOA), total wake time (TWT), sleep onset latency (SOL), total sleep time (TST), and sleep efficiency (SE) (59–62).

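### The NBZDs reduction rate is defined at week 6 only but scheduled at six visits, so the plan supports two different analyses, and the random-intercept one does not fit this outcome

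*Protocol article*

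**What the plan says.** Four places in the protocol article bear on this outcome.

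- **Secondary outcome measures, (3).** The rate is the pre-treatment weekly dose minus the post-treatment weekly dose, divided by the pre-treatment weekly dose, times 100%. A note adds that "post-treatment refers to week 6 of the treatment period". The opening of the same section sends the reader to Table 1 for time points.
- **Table 1.** The row "NBZDs reduction rate" is marked at weeks 0, 2, 4, 6, 8 and 10.
- **Efficacy evaluation criteria, d.** The rate, withdrawal symptoms and craving "will be evaluated using regression-based models appropriate to outcome type, with longitudinal modeling applied where repeated measurements are available".
- **Statistical analysis.** The only longitudinal model named is "linear mixed-effects models with fixed effects for group, time, and group-by-time interaction, and random intercepts for participants". For the other case, "Between-group differences at single time points will be assessed using independent-samples" t-tests or Mann–Whitney U tests.

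The taper shapes the outcome: "NBZDs will be reduced at a rate of 25% of the baseline dose per week", and if withdrawal symptoms are intolerable, "the dose will be temporarily reverted to the previous level".

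**The concern.** The definition gives one value per participant and so leads to a single-time-point comparison. The schedule gives up to six values and so leads to the mixed model. The condition in section d turns on exactly the fact on which the two disagree, so it cannot settle the matter.

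The two analyses are not interchangeable. A random-intercept model with one residual variance assumes the same variance at every visit and the same correlation between any two. The reduction rate cannot satisfy this if the Table 1 visits are all used. Pooling visits with little or no spread with the week-6 visit makes the week-6 standard error too small. The result would be one test that keeps its nominal level and one that is too liberal, with the text allowing either.

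**Working it through.** The plan gives no figure to reproduce here, so the check starts from its formula and schedule.

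**Step 1: what the formula implies.**
- Week 0: (baseline − baseline) / baseline = 0% for every participant, so the variance is exactly 0.
- Week 2: two steps of 25% give at most 2 × 25% = 50%.
- Week 4: 4 × 25% = 100% is first reachable. Reversions keep some participants lower, so by week 6 the rate can lie anywhere from 0% to 100%.

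Unequal variance follows from the formula and the taper alone.

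**Step 2: algebra without a dose-path model.** Let the five later visits each have variance 1 and pairwise correlation ρ, with zeros at week 0. Over six visits the average variance is 5/6. The average covariance over the 15 pairs is 10ρ/15 = 2ρ/3. The random-intercept model's residual variance is therefore 5/6 − 2ρ/3 = 1 − (1 + 4ρ)/6.

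- *Week-6 group difference.* The model uses variance 5/6 where the truth is 1. The large-sample false-positive rate is 2 × [1 − Φ(1.96 × √(5/6))] = 7.4%, whatever ρ is.
- *Week-6-vs-week-0 contrast.* The model uses 2 × residual variance where the truth is 1, so the rate is 2 × [1 − Φ(1.96 × √(2 × residual variance))]:

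| ρ | residual variance | false-positive rate |
|---|---|---|
| 0.5 | 0.500 | 5.0% |
| 0.7 | 0.367 | 9.3% |
| 0.9 | 0.233 | 18% |

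This contrast shows no inflation at ρ = 0.5.

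**Step 3: simulation under assumed dose paths.** From the article: 39 per arm, 25% steps, reversion to the previous level. Assumed: each participant has a beta-distributed weekly chance (concentration 2 or 6) that a step fails; the mean is set so that 10.83%, 30% or 50% are at zero dose in week 6; weekly one-level relapse in weeks 7–10 is 0, 0.1 or 0.2. That makes 3 × 2 × 3 = 18 settings with no true difference, 20,000 trials each.

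SD of the rate: 0 at week 0, 16–20 points at week 2, 29–39 points at week 6.

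| Analysis, nominal 5% | false-positive rate |
|---|---|
| t-test at week 6 | 4.8–5.3% |
| random intercept, six visits, week-6 difference | 8–14% |
| random intercept, week 0 left out, week-6 difference | 5.5–10% |

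A separate, smaller simulation with different dose paths (400 null trials per scenario, Monte Carlo error about 1 to 1.6 points) gave 4.5–6.8%, 9.5–12% and 5.5–9%. At 50% vs 10.83%, its mean model standard error was 5.27 with six visits and 5.77 without week 0, against an empirical 5.93. These are too small by 1 − 5.27/5.93 = 11% and 1 − 5.77/5.93 = 3%.

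**Step 4: how often the choice changes the result.** With weekly relapse 0.1 and week 0 left out, the model and the t-test disagree on significance in roughly 1–4% of null trials (just under 5% in the worst setting) and in about 10% when true success is 20% vs 10.83%. At the planned rates, which "would be 50.00 and 10.83%, respectively", disagreement is about 0.1% or less, with or without week 0.

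**The case against.** A sensible reader can reconcile the text. The explicit week-6 definition together with the conditional clause gives one week-6 regression for the rate and longitudinal models for withdrawal symptoms and craving. The week-0 mark can hardly be a rate and probably means that the baseline dose is collected. Section d also asks for models suited to the outcome type, and covariance structure is usually left to an analysis plan, which is not shown here.

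Part of this stands. Without the week-0 row the misfit is much milder, and the missing covariance detail alone would be no finding. But the same section that defines the rate hands its time points to Table 1, and the only longitudinal model named is the random-intercept one. The contradiction is therefore in the stated text.

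Two stronger readings are tempting and not supported:

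- A reader might take the week-6-vs-week-0 contrast, at 11–23% false positives in the same 18 settings, as the size of the problem. It needs an analyst to enter a column of structural zeros and then test against it. Nothing in the article names that contrast as the test.
- A reader might infer that withdrawal and craving scores cannot be interpreted because no dose is known at weeks 2, 4, 8 and 10. The medication diary is scheduled every week from 0 to 10 and records dose; only the derived percentage is undefined. The article groups the three outcomes under one heading but does not say that one is to be read against another.

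**Conclusion.** The inconsistency is real, and section d does not resolve it. If Table 1 is followed literally, the named model is too liberal for this outcome: about 8–14% false positives at a nominal 5% with six visits, about 5.5–10% without week 0, against about 5% for the week-6 test. That the variance is zero at week 0 is certain. The percentages rest on assumed dose paths that the article does not supply.

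The point is minor. The rate is one of many unranked secondary outcomes, and the article does not single it out as key. The primary outcome and the sample size are untouched. It would also go too far to say that the two analyses often disagree: with week 0 omitted they rarely do under the null, and at the planned effect they practically never do. The choice matters mainly if electroacupuncture has a smaller effect than planned.

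**What to change.** 1. In Secondary outcome measures and Efficacy evaluation criteria, d, name week 6 (days 36–42, the window already used for the primary outcome) as the time point for the between-group test of the reduction rate.
2. In Table 1, relabel the week-0 mark as 'baseline weekly dose', and enter no week-0 rate in any model.
3. Define the rate at weeks 2, 4, 8 and 10 from the diary, using the seven days ending at each visit, and report it descriptively.
4. If a longitudinal model is also fitted, use post-baseline visits with an unstructured covariance, or robust standard errors if that does not converge, instead of random intercepts alone.

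The cost is wording only, since the diary data are already scheduled. The downsides are that an unstructured covariance may fail to converge at 39 per arm if few doses change in weeks 7–10, that robust standard errors are slightly liberal at this size (about 6% in a check of 600 fitted trials), and that a week-6 test does not use weeks 8 and 10.
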